#### Assessment of current attachment style of the PWD

After the interview, family caregivers will be invited to visit their relative. They will meet in a room of the nursing home and the task will be based to some extent upon ‘Ainsworth’s strange situation’, an experimental research setting originally conceived to observe young children. This situation will aim to facilitate exploration of possible attachment behaviours under different conditions. The visit will last about 15 min. There will be four distinctive stages:
The patient is together with the researcher, a trained psychologist in the role of stranger in a room. The family caregiver meets the patient. It is an unexpected visitThe family caregiver indicates, by talking and/or gesturing, that they must leave and suddenly ends the visit. This creates a potentially threatening moment for the PWDThe patient is once again in the room with the strangerThe family caregiver comes back to the room

The whole visit will be video-recorded. The occurrence of attachment behaviours will be determined afterwards by interval sampling. The presence or absence of attachment behaviours will be registered on an observational grid, a non-validated instrument developed for the present study (see Table 2).

We expect the stability of the attachment style of the PWD in term of a correlation between the premorbid attachment style and the current one. We also expect a correlation between the patients’ attachment styles and their response to DTI.

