Another issue is the explanatory model of the DT process. Some authors have applied the concept of attachment theorised by John Bowlby to the ‘doll’ object [15, 17]. Attachment theory holds that the propensity of human beings to seek closeness and protection when feeling vulnerable or frightened is an expression of an innate motivational system. This system activates attachment behaviours directed to achieve proximity and protection from another person (i.e. crying, calling, approaching and holding). The attachment behaviours persist during the entire life cycle, ‘from the cradle to the grave’ [18], and are linked to three types of mental states: secure, insecure and unresolved [19]. This motivational system is particularly relevant for PWD, since dementia often exposes them to feelings of personal vulnerability [20, 21]. The observation of DT interventions revealed that PWD recognised the doll as a real baby and replaced the requests for care and protection (through attachment behaviours, i.e. vocalisations, gestures and tears) with caregiving behaviours (i.e. reassuring and cradling the doll and restoring a sense of calm and peacefulness). The attachment theory could frame the therapeutic function of the doll for PWD in the advanced stages. Such an explanatory model of the DT process has been proposed in a previous study [15], but more robust empirical research is needed in order to confirm it.

In the present single-blind, randomised controlled trial, the first hypothesis regards the 30-day efficacy of the DT on BPSD, professional caregivers’ perceived stress linked to BPSD, patients’ physiological indices of stress, and interactive behaviours. The second hypothesis is that the past attachment styles, embedded during one’s life cycle, are stable even in the advanced stages of dementia. It is also hypothesised that the caregiving behaviours of PWD shown during the doll presentation are linked to their attachment styles.

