### Secondary goal

The secondary goal is the confirmation of the hypothesised stability of the past attachment style of the PWD (provided by the Adult Attachment Interview (AAI) [24] administered to the patients’ offspring (family caregivers), even in the advanced stages of dementia. The current attachment style of the PWD is provided by the observations of the patient during a situation of meeting-separation from their own family caregiver. These evaluations will be conducted, after conclusion of interventions, among a sub-group of participants in the experimental condition. We expect to find an association between the past and the current attachment style of the PWD, categorised as secure, insecure, and unresolved. Furthermore, the relationship between patients’ attachment styles and the response to DTI in terms of caregiving behaviours towards the doll (e.g. caressing the object, talking to it and smiling) will be investigated. We expect that PWD with a previous secure attachment style will accept the doll and will show more caregiving behaviours compared to PWD with insecure attachment style, while these latter will show more rejection, avoidance or excessive caregiving reactions towards the doll. We also expect that PWD with unresolved attachment style will show inconsistent responses to the doll presentation, with approaching and rejecting behaviours.

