### Sample size

To our knowledge, at the start of the study on 1 February 2017, no previous study had measured the efficacy of DT using the NPI-NH score. Therefore, a referral upon existing data could not be used in the power calculation. The power analysis was conducted using an estimated medium effect size (*f* = 0.25), an alpha level of 0.05, and a power of 0.8. According to statistical computing, a sample size of *n* = 128 is required, with 64 participants per group, for an analysis of covariance that includes the NPI-NH baseline score as a covariate. We planned an increase in sample size of 13 participants, because the expected drop-out rate is 10% due to possible acute clinical conditions interfering with the participation in the study, or death. In case of a refusal of the object (doll or cube), another participant will be enrolled as a replacement. Participants who underwent less than 60% of sessions will be excluded from analysis. The power calculation was performed with the programme *G*Power* 3.1 [27].

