### Secondary outcomes

#### Confirmation of stability of attachment style

Assessment of premorbid attachment style of PWD (Adult Attachment Interview (AAI)).

We have planned to study 30 patient-offspring couples (about 47% of the participants in the experimental group). When offspring who regularly visit the patient have accepted the interview, the AAI will be administered to a son or daughter of a patient among those in the DTI group. The AAI is a semi-structured interview designed to evaluate attachment styles in adult populations and allows us to identify three different categories of mental states related to the attachment style of the son or daughter of the PWD: free, dismissing/preoccupied, or unresolved. Free adults have positive internal representations about past relationships with their parents and feel free to explore their infant experience. Dismissing or preoccupied adults (categorised as insecure attachment) fail in telling coherent attachment stories about their parents; they are inclined to idealise or denigrate the role of their parents in the past. Unresolved adults show problems with past mourning experiences and unresolved trauma occurring during infancy. Since a correspondence of 75% between the individual’s attachment and that of their children has been reported [33], we can hypothesise that the AAI is a useful instrument to infer the premorbid attachment style of PWD. This semi-structured interview will be administered in the nursing home and will be video-recorded. The coding of the answers will be carried out by an external trained and authorised psychologist.

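### Attachment-style stability is to be confirmed by a correlation or association between three categories, which does not show that residents keep the same category; agreement should be the criterion

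*Protocol article*

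**What the plan says.** The aim is stability. The Secondary goal section states: "The secondary goal is the confirmation of the hypothesised stability of the past attachment style of the PWD". The Background gives the same hypothesis, beginning "The second hypothesis is that the past attachment styles, embedded during one".

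The criterion is worded differently in two places:
- Secondary goal: "We expect to find an association between the past and the current attachment style of the PWD, categorised as secure, insecure, and unresolved".
- Assessment of current attachment style of the PWD: the expectation is "stability of the attachment style of the PWD in term of a correlation between the premorbid attachment style and the current one".

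The past style is not measured on the resident. It is inferred from the Adult Attachment Interview of a son or daughter, which yields "three different categories of mental states related to the attachment style of the son or daughter of the PWD". The justification given is a parent-child match ("Since a correspondence of 75% between" the individual's attachment and that of their children). The current style comes from a separation-and-reunion observation scored on a grid that the article itself calls non-validated. On size: "We have planned to study 30 patient-offspring couples (about 47% of the participants in the experimental group").

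The Statistical analyses section names no test for this goal. The article nowhere mentions agreement, concordance, kappa or the proportion of residents who keep their category.

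**The concern.** Stability means that a resident classified as secure in the past is classified as secure now, and likewise for the other two categories. Association asks something weaker: whether knowing the past category helps to predict the current one. A consistent move from one category to another satisfies that as fully as no move at all. Correlation has a further difficulty. It needs ordered scores, and the article gives no reason to order the three categories.

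If the criterion were followed as written, the sub-study could report stability as confirmed from data in which many residents had changed category. Such change is not excluded by the article: its Discussion allows that style may alter over life and that later adaptations could be lost in advanced dementia.

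**Working it through.** **Inputs.** There are 30 pairs, 64 participants per arm, three categories, 75% parent-child correspondence and a 0.05 significance level, all from the article. The article gives no category distribution, so the distributions below are assumptions.

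**The plan's own figure.** 30/64 = 46.9%, which reproduces the stated share of about 47%.

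**Formulas for a 3×3 table** (rows past, columns current, order secure / insecure / unresolved, n = 30):
- chi-square = Σ(O - E)²/E on 4 df
- Cramér's V = √(chi-square/(2n))
- agreement po = diagonal sum/n
- chance agreement pe = Σ(row total × column total)/n²
- kappa = (po - pe)/(1 - pe)

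**Constructed tables.**

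| Table | chi-square | p | V | Agreement | kappa |
|---|---|---|---|---|---|
| A. All keep their category: [10,0,0], [0,10,0], [0,0,10] | 60.0 | 2.9e-12 | 1.00 | 100% | 1.00 |
| B. All move in a cycle: [0,10,0], [0,0,10], [10,0,0] | 60.0 | 2.9e-12 | 1.00 | 0% | -0.50 |
| C. 80% keep: [8,1,1], [1,8,1], [1,1,8] | 29.4 | 6.5e-06 | 0.70 | 80% | 0.70 |
| D. 80% move: [1,8,1], [1,1,8], [8,1,1] | 29.4 | 6.5e-06 | 0.70 | 10% | -0.35 |
| E. Milder shift: [3,12,1], [1,2,6], [1,1,3] | 12.1 | 0.016 | 0.45 | 27% | -0.04 |

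For B: V = √(60/60) = 1.00; pe = 3 × (10 × 10)/900 = 0.333; kappa = (0 - 0.333)/0.667 = -0.50.

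For E: po = (3 + 2 + 3)/30 = 8/30 = 0.267. Row totals are 16, 9, 5 and column totals 5, 15, 10, so pe = (80 + 135 + 50)/900 = 0.294 and kappa = (0.267 - 0.294)/0.706 = -0.04. Seven of its nine expected counts are below 5, so the chi-square p is approximate; a permutation test gives about 0.01.

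The association statistics are identical for A and B, and again for C and D. Agreement and kappa separate each pair.

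**Correlation read literally (codes 1-2-3).** Coding exposes the cycle in B (r = -0.50) but not every shift. If 15 residents go from secure to insecure and 15 from insecure to unresolved, r = 1.00 with 0% agreement and kappa = (0 - 0.25)/0.75 = -0.33. Table E gives r = 0.38, p about 0.04.

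**What agreement to expect under true stability.** Suppose every resident is stable, the 75% figure applies to this three-category scheme, and current style is classified without error. Expected agreement is then 0.75. With the same assumed distribution on both sides, and SE ≈ √(0.75 × 0.25/30)/(1 - pe):

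| Assumed distribution | pe | kappa = (0.75 - pe)/(1 - pe) | SE |
|---|---|---|---|
| Equal thirds | 0.333 | 0.63 | 0.12 |
| 50/30/20 | 0.380 | 0.60 | 0.13 |
| 60/25/15 | 0.445 | 0.55 | 0.14 |

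**The case against.** **No test is fixed.** The two sentences are expectations in clinical prose, the Statistical analyses section attaches no coefficient to them, and an analysis plan could still choose kappa. It is true that no coefficient is named, and leaving that choice to the analysis plan would be no fault. But the article does say what stability is to mean, namely correlation or association. An analysis plan built on agreement would depart from that wording, so the wording is what needs changing.

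**The tables are built to make the point.** This stands as a limit. The full cycle requires every resident to move, including from unresolved to secure, and nothing in the article suggests that. A reader might infer that any systematic drift from secure to insecure would come out as significant association. It need not. Keep the drift in table E (12 of 16 secure residents become insecure) but let insecure residents mostly stay ([3,12,1], [1,7,1], [1,1,3]), and p = 0.06 with 43% agreement and kappa 0.17. With [4,12,0], [1,7,1], [0,1,4], the same number of moves gives p = 0.001 and kappa 0.27. So association can be significant under systematic change; it is not bound to be.

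**The Discussion does not predict a secure-to-insecure shift.** Correct. It says only that style may change and that later adaptations could be lost. It names no direction and does not say that the change is systematic across residents.

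**The 75% is not an established ceiling.** Also correct. It comes from a cited source, the article does not say that it holds for these three categories, and the current-style grid is non-validated. With classification error in the grid, agreement under true stability would usually be lower still, by an unknown amount.

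**Conclusion.** The point holds: association or correlation between past and current category does not establish stability. At n = 30 the same chi-square (60.0) and V (1.00) arise with 100% and with 0% agreement, and a less extreme table reaches p = 0.016 with agreement slightly below chance (kappa -0.04).

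The logic does not depend on any assumed distribution; the particular values do. If residents really are stable and the proxy is informative, association should also be present. The flaw is that the converse does not follow.

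The benchmark of about 75% agreement (kappa about 0.55 to 0.63) is conditional on the two assumptions stated with it. Its use is to show that 100% is the wrong yardstick, not to set a threshold.

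The consequence is limited to a secondary goal in a sub-group of one arm. A reader should not carry it over to the efficacy comparison: the ANCOVA and the sample size of 128 are untouched.

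**What to change.** In the Secondary goal section and under the assessment of current attachment style, replace association and correlation as the stability criterion with percent agreement and unweighted Cohen's kappa, each with a 95% confidence interval, on the 3×3 table of past by current style. Keep the association test as supportive only. State in advance what level of agreement will count as stability.

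Add that agreement will be read in light of the proxy. Under the reported 75% correspondence, and assuming it applies to these three categories with error-free current classification, about 75% rather than 100% would be expected if every resident were stable.

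The separate expectation that attachment style relates to the response to the doll can remain an association.

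The cost is a sentence or two of text. The data, assessments and number of pairs stay the same, with no added burden on residents or families.

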### Other variables

Other variables will be collected for the purpose of the present study, as follows: age of the PWD at the time of baseline; baseline Mini Mental State Examination (MMSE) score [34]; total number and relative dosages of psychopharmacological therapies for behavioural and psychiatric symptoms; presence of physical restraints; number of children and monthly visits to the PWD; age and gender of the offspring of PWD. A summary of the assessment performed at each time of the study is reported in Table 3.

**Table 3 Tab3:**
[figure not shown]
Content for the schedule of enrolment, interventions and assessments*

*MMSE* Mini Mental State Examination*, NPI-NH* Nursing Home version of Neuropsychiatric Inventory, *NPI-NH-D* Nursing Home version of NPI Distress, *AAI* Adult Attachment Interview

### Statistical analyses

As a first step, a post hoc evaluation by descriptive statistical comparisons between the intervention and the control groups in age and baseline NPI-NH will be conducted to assess the effectiveness of the randomised assignment. To evaluate associations between biological parameters (decreased, influent, or increased) of each patient at the baseline versus the post intervention, the chi-square test or Fisher’s exact test will be performed. Primary outcomes will be tested performing an analysis of covariance (ANCOVA) of these measurements with the experimental group as the factor baseline NPI-NH and total number and posology of psychopharmacological therapies as the covariates. In order to evaluate how much variance in NPI-NH net change can be explained by groups (experimental versus control groups) after controlling for baseline NPI-NH and biological parameters, a multiple regression analysis will be performed.

Treatment efficacy will be analysed by a per-protocol analysis (PPA) that excludes all drop-outs. Differences will be considered statistically significant when *p* values are lower than 0.05.

All analyses will be conducted using Stata version 13 (Stata Corp., College Station, TX, USA).

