#### Physiological outcomes

We have planned to monitor three physiological outcomes: blood pressure (systolic and diastolic), heart rate and salivary cortisol level. Blood pressure (systolic and diastolic) and heart rate are biomarkers of acute stress involved in the response to physical and psychosocial stressors. Salivary cortisol level is a biomarker of stress, and its secretion is the final product of the activation of stress-response mechanisms; specifically, the hypothalamic-pituitary-adrenal axis [29]. Changes in its secretion rate were reported during acute responses to stress in the context of illnesses and in cognitive impairment [30], in mood disorders [31] and in individuals with different adult attachment styles [32]. Professional caregivers will collect the saliva samples, blood pressure (systolic and diastolic) and heart rate readings of each participant in both the experimental and control groups, immediately before the treatment and 15 min after the end of treatment at the first and the 30th session of DTI or SI. We expect a significant difference between the experimental and the control group in blood pressure levels and heart rate from the first to the 30th session. A ratio between pre-treatment versus ‘after 15 min’ will be calculated for the first and 30th sessions. We expect a significant difference in the concentration of salivary cortisol between the experimental and control groups from the first to the 30th sessions.

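### The chi-square/Fisher test on three-level biological categories tests neither within-patient change nor the doll-versus-cube difference, and the plan does not say whether it or the ANCOVA decides the physiological outcomes

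*Protocol article*

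**What the plan says.** Blood pressure, heart rate and salivary cortisol appear in the Physiological outcomes subsection, which sits under Primary outcomes. They are recorded "immediately before the treatment and 15 min after the end of treatment at the first and the 30th session of DTI or SI". The hypotheses concern the arms: a "difference between the experimental and the control group in blood pressure levels and heart rate from the first to the 30th session" and, for cortisol, "We expect a significant difference in the concentration of salivary cortisol between the experimental and control groups from the first to the 30th sessions". A continuous summary is also defined: "A ratio between pre-treatment versus ‘after 15 min’ will be calculated for the first and 30th sessions".

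The Statistical analyses section then says three things that touch these measures:

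- A categorical test: "associations between biological parameters (decreased, influent, or increased) of each patient at the baseline versus the post intervention, the chi-square test", with Fisher's exact test as the alternative. The sentence gives no arm, no cut-offs and no paired method.
- An arm comparison: "Primary outcomes will be tested performing an analysis of covariance (ANCOVA) of these measurements with the experimental group as the factor". The covariates named are baseline NPI-NH and psychotropic medication (number and dose).
- A multiple regression of NPI-NH change in which the biological parameters are adjusted for, not tested.

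**The concern.** The hypothesis is a difference between two randomised groups on measured quantities. The only sentence that names the biological parameters as the thing tested compares each patient with herself, in three categories, without reference to group. A chi-square test of independence on such data does not estimate an arm effect. Depending on the table intended, it may not address change over time either.

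The plan treats any p value below 0.05 as significant. A significant chi-square on these data could therefore be reported as a physiological benefit of the doll when it shows only that patients who reacted one way at session 1 tended to react the same way at session 30. Because these measures are listed as primary, it should be settled before analysis which test carries the conclusion.

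**Working it through.** **The plan's own figure.** Inputs from Sample size: f = 0.25, alpha 0.05, power 0.80, one covariate, two groups. With noncentral F, lambda = f² × N = 0.0625 × 128 = 8.0 and df = 1 and 128 − 3 = 125, power is 0.801. The stated 128 (64 per group) reproduces. For two equal groups d = 2f = 0.5, which is used below.

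**Assumptions not in the documents.** Underlying values are normal. They are cut into three categories at ±0.43 SD, which makes thirds of about 0.334, 0.333 and 0.334. Within-patient correlation between sessions is 0.3 to 0.5 (other values where stated). I take the middle category to mean unchanged.

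The sentence permits three table layouts.

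**Layout A: session-1 category by session-30 category, one patient per cell (3 × 3, 4 df).** The noncentrality is N × Σ(p_ij − p_i·p_·j)² / (p_i·p_·j), with cell probabilities from the bivariate normal. N = 128, no change over time and no arm effect.

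- Correlation 0.3: the sum is 0.0582; 128 × 0.0582 = 7.45; probability of p < 0.05 is 0.57.
- Correlation 0.5: the sum is 0.1711; 128 × 0.1711 = 21.9; probability 0.98.
- Simulation (4,000 trials per setting) agrees: 0.56 to 0.58 at correlation 0.3, about 0.98 at 0.5, and about 0.05 at zero.
- A uniform 1 SD fall with zero correlation gives about 0.05, so the test does not respond to a real shift.

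**Layout B: time by category, each patient counted twice (2 × 3).** With no true change, rejection is below the nominal 5%.

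| n | corr. 0.3 | corr. 0.5 | corr. 0.7 |
|---|---|---|---|
| 64 | 3.2% | 2.3% | 0.9% |
| 128 | 2.9% | 2.0% | 1.1% |

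For a 0.5 SD shift at n = 64 and correlation 0.5, power is 60%, against 80% for the Stuart–Maxwell test of paired change. This layout still has no arm comparison.

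**Layout C: arm by change category (2 × 3, 2 df).** The text does not state this layout. With d = 0.5, 64 per arm and cuts at ±0.43 SD, the category probabilities are 0.334, 0.333, 0.334 in one arm and 0.528, 0.296, 0.176 in the other. The noncentrality is 128 × 0.0473 = 6.05 and power is 0.59. Moving the cuts from ±0.25 to ±1.0 SD gives 0.56 to 0.60. A t test on the measured values has 0.80 to 0.81. The loss is about 20 percentage points.

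**Summary.** A tests consistency, B tests change inefficiently and ignores arm, and C would test the arm difference with reduced power.

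**The case against.** The strongest reply is that the chi-square sentence is not the efficacy analysis. It speaks of associations, and the next sentence gives an ANCOVA with group as factor for the primary outcomes, which by heading include the physiological ones. This stands, and it limits the point. A reader might infer that the plan has no between-arm test of physiology and throws away the measured values. That describes one sentence, not the plan.

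Two further inferences should also be resisted.

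- That the test treats paired data as independent. This is so only under layout B, where the error is conservative. Under layout A each patient occupies one cell, and chi-square is a valid test of association that answers a different question.
- That 57% to 98% are false-positive rates. At a non-zero correlation the null of independence is false, so these are rates of detecting a real association. They become misleading only if the result is read as a treatment effect.

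It is also fair that a condensed article may leave cut-offs and table layout to a fuller document. I do not rest the point on those omissions.

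The reply does not remove the mismatch. The article states a test that, as worded, does not match its own hypothesis. It also states an ANCOVA whose named covariates would adjust blood pressure, heart rate or cortisol for baseline NPI-NH and not for the measure's own starting value. It does not say which of the two analyses decides these outcomes.

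**Conclusion.** The point holds as a mismatch between a stated test and a stated hypothesis, together with an undeclared choice between two analyses of the same outcomes. It does not show that the arm comparison is missing from the plan.

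The cost of using the categories for the arm comparison is firm: power of about 0.60 or less against 0.80, at the trial's own sample size and effect size and over a wide range of cut-points. The 57% to 98% range depends on layout A and on assumed correlations of 0.3 to 0.5; it falls to about 5% at zero correlation. What does not depend on those assumptions is the rule for interpretation: a significant result from this test, in a table without arm, is not evidence of efficacy.

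**What to change.** 1. Drop the chi-square/Fisher test as an inferential analysis. Keep the three categories only as a descriptive table by arm, with cut-offs defined.
2. State that the between-arm ANCOVA on continuous values is the analysis of each physiological outcome.
3. Adjust like for like: the session-30 reading for the same reading at session 1 and, for the post/pre ratio, the log session-30 ratio for the log session-1 ratio. Analyse cortisol on the log scale. Say which of the two readings per session is meant.
4. Report the arm difference with its 95% confidence interval.

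The session-1 reading taken after treatment, and hence the session-1 ratio, already follows one exposure to the object. Adjusting for either matches the plan's own contrast from first to 30th session and estimates the arm difference beyond the first-session response. The text should say so.

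The cost is wording and minor analysis work. All the readings needed are already in the plan, and the sample size is unaffected.

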#### Professional caregiver distress outcome

A decrease of the professional caregiver distress ratings related to the patient’s BPSD is also expected. It will be measured as the net change in the NPI-NH-D total score from baseline to post intervention [22, 23]. We expect a significant difference in NPI-NH-D total scores between the experimental and active control groups. It will be administered to the staff by a trained blinded psychologist. The time frame of that evaluation is from baseline (T0) to 30 days after the beginning of the intervention (T2).

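### The one ANCOVA covariate set suits NPI-NH total, but for NPI-NH-D and the physiological outcomes it omits the outcome's own baseline, at some cost in precision

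*Protocol article*

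**What the plan says.** The Primary outcomes part of the protocol article covers NPI-NH total, NPI-NH-D total, blood pressure, heart rate, salivary cortisol and interaction with the object. The Statistical analyses section tests the primary outcomes, in the plural, with a single ANCOVA: "with the experimental group as the factor baseline NPI-NH and total number and posology of psychopharmacological therapies as the covariates". The punctuation is faulty. On any reading, though, baseline NPI-NH is the only baseline of an outcome in the model.

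The Sample size section says that "a sample size of *n* = 128 is required, with 64 participants per group". That figure belongs to an ANCOVA adjusted for baseline NPI-NH, so only NPI-NH is sized.

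For caregiver distress the article says "It will be measured as the net change in the NPI-NH-D total score from baseline to post intervention", so a T0 value exists. Saliva, blood pressure and heart rate are taken "immediately before the treatment and 15 min after the end of treatment at the first and the 30th session". Blood pressure and heart rate are compared between arms from the first to the 30th session, and a ratio of the pre-treatment to the 15-minute value is calculated at each of the two sessions. The Statistical analyses section also gives biological parameters a categorical analysis by chi-square or Fisher's exact test. The Discussion says that no basal stress level is collected before the intervention can interfere.

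**The concern.** ANCOVA gains precision, and protects against chance imbalance, mainly because the covariate predicts the outcome. The best single predictor is usually the same measure taken before treatment. Here the covariate was evidently chosen for NPI-NH total and then carried over to outcomes for which it is at best a proxy.

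Defining the outcome as a change does not repair this. Subtracting the baseline fixes its slope at 1. With equal variances the best slope is the baseline-to-follow-up correlation, which is below 1. Subtraction therefore over-corrects: the arm that happens to start higher tends to show the larger fall, and the estimate moves with the imbalance. At stake are wider confidence intervals than the collected data allow, and estimates for distress and the physiological measures that partly reflect the draw of the randomisation.

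**Working it through.** **The plan's own figure.** The inputs are an "estimated medium effect size (*f* = 0.25") and "an alpha level of 0.05, and a power of 0.8". A noncentral F test with 1 numerator degree of freedom and noncentrality 0.25² × 128 = 8 gives power 0.801 at N = 128, with 0, 1 or 3 covariates. The stated 64 per group reproduces. For NPI-NH total the point changes nothing.

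**Assumptions for the other outcomes.** The documents give neither SDs nor correlations, so these are mine:
- outcome variance is 1 at both times;
- r is the correlation of own baseline with follow-up, 0.3 to 0.7;
- q is the correlation of baseline NPI-NH with the own baseline, 0 to 0.8;
- baseline NPI-NH relates to follow-up only through the own baseline, so that correlation is rq;
- the drug covariates are left out of the comparison.

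**Residual variances.**
- Own-baseline ANCOVA: 1 − r².
- Change score adjusted for baseline NPI-NH: 2(1 − r) − [q(1 − r)]².
- Raw follow-up value adjusted for baseline NPI-NH: 1 − (rq)².

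At q = 0 the ratio of the second to the first is 2(1 − r)/(1 − r²) = 2/(1 + r). For r = 0.5 and q = 0.3 the change score gives 1 − 0.15² = 0.978, against 1 − 0.25 = 0.75, a ratio of 1.30.

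**Power.** The effect is set so that own-baseline ANCOVA has 80% power at N = 128 (f = 0.25 on its residual scale). Under the written covariates f becomes 0.25 × √(own/change). The last column is the total N that would restore equal precision (128 × ratio).

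| r | q | own | change | ratio | power | N |
|---|---|---|---|---|---|---|
| 0.3 | 0 | 0.91 | 1.400 | 1.54 | 0.619 | 197 |
| 0.3 | 0.3 | 0.91 | 1.356 | 1.49 | 0.633 | 191 |
| 0.3 | 0.8 | 0.91 | 1.086 | 1.19 | 0.729 | 153 |
| 0.5 | 0 | 0.75 | 1.000 | 1.33 | 0.681 | 171 |
| 0.5 | 0.3 | 0.75 | 0.978 | 1.30 | 0.691 | 167 |
| 0.5 | 0.8 | 0.75 | 0.840 | 1.12 | 0.756 | 144 |
| 0.7 | 0 | 0.51 | 0.600 | 1.18 | 0.735 | 151 |
| 0.7 | 0.3 | 0.51 | 0.592 | 1.16 | 0.741 | 149 |
| 0.7 | 0.8 | 0.51 | 0.542 | 1.06 | 0.777 | 137 |

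If the ANCOVA is instead run on the raw follow-up value, the ratio is 1.04 to 1.96 and power 0.79 to 0.52.

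**Dependence on chance imbalance.** With 64 per arm the baseline difference between arms has SD √(2/64) = 0.177, so 95% of draws lie within 1.96 × 0.177 = 0.35 SD. Take an imbalance of 0.3 SD that baseline NPI-NH does not explain. A change-score estimate is then off by (r − 1) × 0.3 = −0.21, −0.15 or −0.09 SD at r = 0.3, 0.5 or 0.7. Own-baseline ANCOVA is off by 0.

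**Simulation** (6000 runs, 64 per arm, r = 0.5, q = 0.3):

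| Analysis | Correlation of estimate with imbalance | Power | Type I error |
|---|---|---|---|
| Change, adjusted for NPI-NH | −0.47 | 0.68 | 0.056 |
| Follow-up, adjusted for NPI-NH | +0.44 | 0.68 | 0.052 |
| Own-baseline ANCOVA | −0.03 | 0.79 | 0.057 |

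Type I error is about 5% in all three.

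**The case against.** The strongest reply is that the outcome that matters is handled correctly. The Behavioural outcome section speaks of the NPI-NH change in the singular as the primary outcome, the trial is sized on it, and its own baseline is in the model. A reader might infer from the single specification that every primary outcome is wrongly adjusted. The documents do not support that: NPI-NH total is not affected. Nor is object interaction, which is first recorded with the object already presented and so has no pre-exposure value to adjust for.

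A reader might also infer that baseline differences in the other outcomes go uncorrected, or that the tests are invalid. Neither follows. The own baseline enters by subtraction or division, what remains is over-correction, and under randomisation the type I error is kept.

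Three objections narrow the physiological part. The formulas above describe a difference score, not the pre/post ratio. The biological parameters also have a categorical analysis, so it is unclear how far the ANCOVA is their main test. The Discussion says that no basal stress level is collected. These limit the claim but do not remove it. The pre-treatment reading at session 1 precedes the first presentation of the object, in women with no previous doll therapy, and nothing in the article puts it into the ANCOVA.

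The size is also open to challenge. The 80% reference is hypothetical, since the article claims no power for these outcomes. Zero correlation with baseline NPI-NH is implausible for NPI-NH-D, which rates distress over the same symptoms. Both objections stand, and the range has to be read with them.

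Lastly, the article is a condensed text and an SAP not shown may give outcome-specific models. But the covariates are stated here, so the point is about a stated rule, not about missing detail.

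**Conclusion.** The point holds for NPI-NH-D, and for blood pressure, heart rate and cortisol to the extent that they are tested by this ANCOVA. It is a loss of efficiency and of accuracy given the baseline draw, not an error in the test, and it does not touch the outcome on which the trial is sized.

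Under the assumed correlations a change score has 1.06 to 1.54 times the variance of an own-baseline ANCOVA, and an outcome that would have 80% power has about 78% to 62%. For NPI-NH-D the loss is probably near the small end: 1.06 to 1.19 times the variance if its baseline correlates 0.8 with baseline NPI-NH, itself an assumption. No size can be given for the pre/post ratio. The change is worth making because it costs nothing, but the trial's main conclusion does not depend on it.

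**What to change.** Replace the single covariate set by one rule, fixed before the data are analysed: each outcome is adjusted for its own pre-intervention value.
- NPI-NH total: T0 NPI-NH, as now.
- NPI-NH-D: T0 NPI-NH-D. The outcome may stay a net change; once its own baseline is a covariate, the treatment estimate equals that from the follow-up value.
- Blood pressure, heart rate and cortisol (cortisol on the log scale if preferred, at both times): the 30th-session value, adjusted for the same measure's pre-treatment reading at session 1. State which 30th-session reading is analysed, and whether this ANCOVA or the categorical comparison is the main test.

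Baseline NPI-NH may stay as an additional covariate for all of them. Object interaction needs no change on this point. The cost is a sentence or two in the analysis section or the SAP; every value needed is already scheduled for collection.
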